### Cognitive: concentration, distractedness, and focus

To assess concentration, distractedness, and focus, three items will be rated on a 5-point Likert scale (1 = *very slightly or not at all*, 5 = *extremely*). Participants will be asked “At the moment you received the text message from us, what were you doing?” Participants will then be asked to rate their concentration, distractedness, and focus. The three items were adapted from previous research [105]. A total mean score will be calculated.

Behavioral: Eating, caffeine, alcohol, nicotine, marijuana, opioids, prescription and over the counter (OTC) stimulants, and sleep aids

To assess behaviors related to substances, including food/drinks [106] and drugs, participants will report their daily frequency and intake of each. For example, participants will be asked “At the moment you received the text message from us, were you drinking a beverage?” Participants will then be asked to indicate which drink(s) they were consuming. An average weekly frequency and intake of each substance will be calculated. Additionally, participants will be asked to list the use of additional psychoactive drugs (e.g., cocaine, heroin).

### Social: the positivity ratio

To assess social activity, three items will assess if the participant is with anyone at the time of the EMA. Additionally, the Positivity Ratio (see EMA for Emotion domain) will be calculated when the participant is alone, with a family member, or with a friend.

### Physical: activity and sedentary behaviors

To assess physical activity for the day, one item will be rated on a 2-point Likert scale (yes, no). The question, “Were you physically active today?” has been used in previous research [107, 108].

#### Other measures

##### Adapted self-report habit index – secondary bundle to build (Adapted SRHI—Secondary)

The Adapted SRHI—Secondary will assess the habit strength of the secondary bundle to build at each session during treatment, post-treatment, 6-month, and 12-month follow-up assessments. This measure is comprised of 1-item from the original Self-Report Behavioral Automaticity Index. Based on previous research [70], the 1-item selected, “I do automatically,” has been shown to have adequate face validity based on expert ratings. The 1-item will be rated on a 5-point Likert scale (1 = *strongly disagree*, 5 = *strongly agree*), where higher scores indicate greater habit strength.

##### Adapted version of the work and social adjustment scale items (Adapted WSAS items)

This measure is described above. It is also included as an “other outcome” as we will also report the five individual item scores.

##### Sleep diary and actigraphy

The Sleep Diary has been described above and will also be used to calculate additional consensus sleep diary variables, including total sleep time, bedtime, and wake-time, calculated separately for weekdays and weekends. Actigraphy (Actiwatch® GT9X Link; Philips Respironics) has been described above and will assess sleep parameters, including sleep onset time, sleep offset time, and total sleep time, calculated separately for weekdays and weekends.

##### Adapted authenticity scale

An adapted version from previous research [109] of the original Authenticity Scale [110] will assess state authenticity. The four items will each be rated on a 7-point Likert scale (1 = *strongly disagree*, 7 = *strongly agree*). Total mean scores range from 1 to 7, where higher scores indicate greater authenticity. This measure will function as a divergent validity measure when assessing the psychometric properties of the Adapted WSAS.

##### Adapted credibility expectancy questionnaire (Adapted CEQ)

The Adapted CEQ will assess the participants’ perception of treatment credibility and expected improvement at the second session during treatment. The 6-item Credibility Expectancy Questionnaire (CEQ) [111] was adapted to include the first four items, assessing the credibility factor fully and the first item of the expectancy factor. In total, four items will be rated via a combination of three 9-point Likert scales (1 = *not at all logical/not at all successful/not at all confident*, 9 = *very logical/very successful/very confident*) and one 0–100% scale. Scores from all items will be converted to standardized *z*-scores, and then a total sum CEQ score will be derived, in addition to separate sum scores for the credibility and expectancy factors. Higher scores indicate that the treatment was evaluated as more credible and expected improvement.

##### Adverse events checklist

The Adverse Events Checklist will assess adverse events experienced during the intervention at the post-treatment assessment. The 16 items, adapted for this study from prior research [112, 113], will each be rated on a 2-point Likert scale (yes, no).

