### Measures

In addition to the measures below, a sociodemographics form is completed by participants at the pre-treatment assessment. Only measures that will be analyzed for the main aims of the study are reported below (see Aims section). The schedule for administering the measures is in Table 4. Unless otherwise specified, the measures below will be administered at the pre-treatment, post-treatment, 6-month follow-up, and 12-month follow-up assessments. To see which measure is associated with each outcome (i.e., utilization, habits, sleep and circadian functioning, and health-relevant domains) see Table 5.

**Table 4 Tab4:** Timeline of measures

		**Pre-treatment**	**Treatment**	**Post-treatment**	**6-month follow-up**	**12-month follow-up**
	Sociodemographics	X				
**Primary**	Utilization Scale	X		X	X	X
	SRBAI-US	X		X	X	X
	CSHS	X		X	X	X
	CSM	X		X	X	X
	PROMIS-SRI	X		X	X	X
	PROMIS-SD	X		X	X	X
	Adapted WSAS Total Score	X		X	X	X
**Secondary**	Adapted SRHI – Primary Bundle		X	X	X	X
	PSQI	X		X	X	X
	Sleep Diary^a^	X	X	X	X	X
	Actigraphy^a^	X		X		
	DASS	X		X	X	X
	PROMIS-CF	X		X	X	X
	BSSS	X		X	X	X
	PROMIS-APS	X		X	X	X
	PHQ	X		X	X	X
	EMA Composite Risk Score^b^	X		X		
**Other**	Adapted SRHI – Secondary Bundle		X	X	X	X
	Adapted WSAS^c^	X		X	X	X
	Sleep Diary^d^	X	X	X	X	X
	Actigraphy^e^	X		X		
	Adapted Authenticity Scale	X		X	X	X
	Adapted CEQ^f^		X			
	Adverse Events Checklist			X		
	Proportion of Text Messages Read^g^		X			

*Note.* SRBAI-US Adapted Self-Report Behavioral Automaticity Index integrated with the Utilization Scale , CSHS Composite Sleep Health Score, CSM Composite Scale of Morningness, PROMIS-SRI PROMIS Sleep-Related Impairment Scale, PROMIS-SD PROMIS Sleep-Disturbance Scale, Adapted WSAS Adapted Version of the Work and Social Adjustment Scale, Adapted SRHI – Primary Bundle Adapted Self-Report Habit Index – Primary Bundle to Build, PSQI Pittsburgh Sleep Quality Index, DASS Depression, Anxiety, and Stress Scales, PROMIS-CF PROMIS-Cognitive Function Scale, BSSS Brief Sensation Seeking Scale, PROMIS-APS PROMIS-Ability to Participate in Social Roles & Activities Scale, PHQ Physical Health Questionnaire, EMA Ecological Momentary Assessment, Adapted SRHI – Secondary Bundle Adapted Self-Report Habit Index – Secondary Bundle to Build, Adapted CEQ Adapted Credibility Expectancy Questionnaire

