### Procedure

We will recruit participants within the USA and Canada, with by far the most participants from the former. Recruitment efforts will include distribution of information about the study to doctors and health care clinics as well as advertisements in the community (e.g., outpatient medical and mental health clinics in the San Francisco Bay Area) and online (e.g., Facebook, Reddit, and Instagram). People who are interested in learning more will be directed to contact the UCB research staff directly by phone or email.

Prospective participants will verbally consent to an initial eligibility phone screen. If the participant is eligible to participate in the full study, they will be invited to the pre-treatment assessment. Informed consent will be obtained prior to starting the pre-treatment assessment via HIPAA-compliant DocuSign, mail, or in-person, if the participant prefers. The pre-treatment assessment will be completed virtually (i.e., phone or HIPAA-compliant Zoom). Informed consent and assessments will be conducted by assessors (i.e., UCB research staff). Assessors enter anonymized data collected from the pre-treatment assessment via a HIPAA-compliant Qualtrics survey.

Once the participant is enrolled, they will be randomly allocated to HABITs or HABITs + Texts (see Allocation section for more details). Both intervention arms include HABITs, which involve three 50-min individual weekly sessions followed by six 30-min individual weekly sessions. Sessions are completed virtually via HIPAA-compliant Zoom. Treatment is delivered by sleep coaches (i.e., UCB research staff who are trained and supervised by [name], [name], MD, and [name]). Only the HABITs + Texts group will receive the text messaging intervention. Text messages will be delivered for 6 weeks. The text messages are collaboratively written by the participant and the participant’s sleep coach (and reviewed and approved by [name] or MD). During treatment, sleep coaches will assist participants in completing treatment assessments using HIPAA-compliant Qualtrics.

At the conclusion of treatment, typically within 8–11 weeks, the post-treatment assessment will take place within 2 weeks of the final session. The follow-ups will take place 6 months and 12 months after the pre-treatment assessment. The post-treatment assessment, 6-, and 12-month follow-ups will be completed by assessors via phone or HIPAA-compliant Zoom, and anonymized data will be entered via HIPAA-compliant Qualtrics.

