### Data management and dissemination

All participant-identifiable data will be saved by the assessment team on a secure password-protected and HIPAA-compliant website. All participants will be assigned identification numbers. These identification numbers will then be used to link anonymized data that is collected via password-protected and HIPAA-compliant Qualtrics. When collecting assessments, assessors will enter the data into HIPAA-compliant Qualtrics. Participant-identifiable data is not shared with outside entities during or after the trial.

A Data Safety Monitoring Board (DSMB) has been formed to help prevent and manage adverse events. The DSMB will be convened on a bi-annual basis for the first year and annually thereafter. For each report, the number of participants screened, the number of participants entered, the number of participants dropping out with the reasons for discontinuing, participant descriptive information, and the number of adverse events or serious events will be reported. All adverse events or serious events will be reported to CPHS (i.e., Institutional Review Board), the DSMB, and NICHD. However, if safety issues arise, this schedule will be changed to monthly meetings. For each report, minutes will be kept.

Organizations not directly involved in the trial (e.g., NICHD, DSMB, Institutional Review Board) have the right to audit and, if such a situation arises, will determine the frequency and procedures for auditing. The project management team will regularly audit the monthly enrollment as well as the completeness and quality of the data.

Results from the trial, as well as analysis code, will be shared via peer-reviewed publications, professional conference presentations, and a summary newsletter for participants. Other than the authors and compliance with data-sharing agreements stipulated by the National Institutes of Health, no other entities have contractual agreements to access the final dataset.

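### The one adverse-event checklist the article describes is given only at post-treatment, so participants lost to the study before that visit have no checklist data

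*Protocol article*

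**What the plan says.** The Adverse events checklist section, under Other measures, gives one administration: "The Adverse Events Checklist will assess adverse events experienced during the intervention at the post-treatment assessment". The 16 items are answered yes or no. In Table 4 (Measures) the row "Adverse Events Checklist" has one mark, under post-treatment. It has none under treatment, 6 months or 12 months.

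Under Procedure, treatment typically ends within 8 to 11 weeks, and "the post-treatment assessment will take place within 2 weeks of the final session". Assessors do that visit, and Allocation says they are blind to arm. Of the sessions themselves, Procedure says: "During treatment, sleep coaches will assist participants in completing treatment assessments using HIPAA-compliant Qualtrics".

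The Sensitivity analyses section plans a set of analyses of Aims 1–3 that accounts for adverse events experienced during the intervention. The Dropout section provides for losses after randomisation, and for losses after treatment but before the post-treatment assessment.

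Safety oversight is described separately, under Data management and dissemination: "A Data Safety Monitoring Board (DSMB) has been formed to help prevent and manage adverse events". All adverse or serious events go to the ethics committee, the board and the funder. Each board report lists dropouts with their reasons.

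**The concern.** Table 4 has a treatment column, which the sleep diary, the habit indices, the credibility questionnaire and the text-reading item use. The checklist is not in it. Its timing is therefore a stated choice and not a gap left by condensing the protocol.

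Two things follow if the schedule is carried out as written.

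- **Missing forms may not be missing at random.** Participants who leave the study before the visit contribute no checklist. If some of them leave because of something the checklist asks about, the forms in hand understate how common events were. The sensitivity analysis would then lack its adverse-event variable for some of the participants it is meant to inform.
- **Recall is long.** One yes/no form covers the whole treatment. Most of the symptom and behaviour scales in the article look back 7 days, and the longest stated windows are 4 weeks or a month.

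At stake are the completeness of the checklist summaries and the meaning of one sensitivity analysis. The main efficacy comparisons are not affected.

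**Working it through.** **Inputs from the article.** Sample size: 128 needed, 20% attrition allowance, 160 recruited. Allocation: 1:1. Procedure: treatment typically 8 to 11 weeks, visit window 2 weeks.

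**Step 1: reproduce the plan's figure.** 128 / (1 − 0.20) = 160, which matches. The allowance corresponds to 160 × 0.20 = 32 participants.

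**Step 2: participants with no checklist.** The article does not say how much of the 20% falls before post-treatment; follow-up runs to 12 months. With q the assumed share lost before the visit, the number without a form is 160 × q:

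- q = 5%: 8
- q = 10%: 16
- q = 20%: 32 (all planned attrition early, about 16 per arm if balanced)

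**Step 3: recall length.** For an event at the very start of treatment, the look-back runs from about 8 weeks (8 + 0) to about 13 weeks (11 + 2). The upper figure combines the longest typical treatment with the last day of the window.

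**Step 4: possible understatement.** The article gives no event rates, so these are assumptions. Let attenders have event risk 20% and those lost have r times that risk. Then:

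- share of affected participants missed = rq / (rq + 1 − q)
- true risk = 20% × (1 − q + rq), against a reported 20%

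With r = 1, the reported risk is unbiased and the share missed equals q: 5%, 10% or 20%.

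With r = 2 (40% among those lost):

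- q = 5%: 3.2 of 33.6 affected missed, about 10%; true risk 33.6/160 = 21%
- q = 10%: 6.4 of 35.2 missed, about 18%; true risk 35.2/160 = 22%
- q = 20%: 12.8 of 38.4 missed, about 33%; true risk 38.4/160 = 24%

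**Step 5: uncommon events.** The chance of seeing at least one case in an arm is 1 − (1 − p)^m, where p is the event risk and m the number of forms. With p = 2% it is 80% for m = 80 and 73% for m = 64. With p = 5% it is 98% and 96%. If losses are unrelated to events, the cost is therefore small; the problem is selective loss.

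**The case against.** The strongest objection is that this form need not be how the trial monitors safety. The Measures section says it lists only measures analysed for the main aims, so an event log would not appear in Table 4. Participants have nine weekly sessions with supervised coaches, an evident route for events to surface. The article condenses a full protocol that is not shown, and elicitation between visits may be described there. All of this stands. It means the checklist can be called only the one systematic inquiry that the article describes.

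A reader might infer that the board sees events only once treatment is over. The article does not support that. Its reporting rule covers all adverse or serious events, is not tied to the checklist, and sets no delay. Routine meetings are spaced ("The DSMB will be convened on a bi-annual basis for the first year and annually thereafter"), but there is an escalation: "However, if safety issues arise, this schedule will be changed to monthly meetings".

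A reader might also infer that everyone who stops sessions is missed. That does not follow either. The analysis of Aims 1–3 keeps all randomised participants whatever their adherence, and nothing bars a person who stops sessions from the post-treatment visit. The gap concerns those lost to the study before it.

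The objection that the sizes are assumed is also right: 32 is a ceiling, and the event rates have no source. Nor does the article plan a formal comparison of events between arms.

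None of this supplies checklists for participants lost before post-treatment, or shortens the look-back.

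**Conclusion.** The point holds as a limited fault in data collection. As scheduled, participants lost before post-treatment have no adverse-event checklist: 8, 16 or 32 of 160 under assumed early losses of 5%, 10% or 20%. Whether this biases the summaries depends on whether leaving is related to events, which the article cannot show. If those lost had twice an assumed 20% risk, about 10% to 33% of affected participants would be missed across that range; with equal risk, the reported rate would be unbiased. The one-third figure needs both the doubled risk and all planned attrition before the visit, and should not be cited alone.

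This is not a failure of safety oversight, and the checklist and board sections do not contradict each other. The change is worth making because it is cheap and acts directly on the selective loss.

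**What to change.** 1. Keep the post-treatment checklist for everyone, completed with blinded assessors. This preserves one comparable measure across arms and across participants already past treatment.
2. Add the same 16 items at the contact when a participant withdraws, completed by an assessor. Amend Table 4 and the checklist section to match.
3. Report, by arm, how many randomised participants have no checklist. Present the adverse-event sensitivity analysis with that number stated and interpret it as conditional on having a form.
4. Optionally, add a short version covering the time since the last session to the Qualtrics form already used in sessions. Analyse it separately, because coaches know the arm and answers given to them may differ from those given to a blinded assessor.

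The cost is a small form and schedule change, with no new staff or visit; the optional session version adds a little burden each week. Some who leave cannot be reached, so the gap will shrink but not close. Recruitment began in May 2022, so participants already past treatment have only the single form and the report should say so.

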The accumulated body of science on habits offers exciting opportunities for improving interventions like TranS-C [41–43]. “Habit” is defined as a process whereby contextual cues, via repetition and reward, come to automatically trigger an impulse to engage in a specific behavior [44–46]. “Habitual behavior” is defined as any behavior triggered by the habit process. To form a habit, a behavior must be repeated after exposure to a stable contextual cue [47, 48]. This strengthens a behavior-context association, to the extent that subsequently encountering the contextual cue triggers an unconscious impulse to engage in the habitual behavior, which in turn translates into the activation of behavior, with little prior thought or conscious intention [41]. The impact of repetition on habit formation is strengthened by rewards, such that repeating more rewarding behaviors causes more rapid or stronger habit formation compared to less rewarding behaviors [49, 50]. Overall, habit promotes frequent engagement in behavior [51–54]. By virtue of their automaticity, habitual behaviors are thought to persist over time, potentially even when people lack motivation to perform them [55]. Habit formation is thus a key mechanism for maintaining behavior change [56]. By integrating the science on habits with behavior change interventions like TranS-C, the aim of the study described herein is to help participants turn new behaviors into habits and thereby increase the benefits of an intervention in both the short and longer term [42, 55]

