## Aims

This randomized controlled two-arm parallel group superiority study with 1:1 allocation ratio will be conducted with young adults who are 18–30 years of age, exhibit an eveningness chronotype, and demonstrate elevated symptoms in one of the five health domains. Participants will be randomized (1:1) to HABITs alone or HABITs plus Text Message Intervention (HABITs + Texts). There are three aims.

Aim 1 is to assess if adding a text message intervention to HABITs improves sleep health behaviors in the short (post-treatment) and longer term (6-month and 12-month follow-up), relative to HABITs alone. Hypothesis 1 is that, relative to HABITs, participants in HABITs + Texts will (a) report utilizing more sleep health behaviors and (b) establish stronger sleep health behavior habits. We hypothesize that these effects (1a and 1b) will be observed from pre-treatment to post-treatment, pre-treatment to 6-month follow-up, and pre-treatment to 12-month follow-up.

Aim 2 is to assess if adding a text message intervention to HABITs improves sleep and circadian functioning in the short (post-treatment) and longer term (6-month and 12-month follow-up), relative to HABITs alone. Hypothesis 2 is that, relative to HABITs, participants in HABITs + Texts will exhibit improved sleep and circadian functioning. We hypothesize that this effect will be observed from pre-treatment to post-treatment, pre-treatment to 6-month follow-up, and pre-treatment to 12-month follow-up.

Aim 3 is to assess if adding a text message intervention to HABITs improves functioning in the five health-relevant domains in the short (post-treatment) and longer term (6-month and 12-month follow-up), relative to HABITs alone. Hypothesis 3 is that, relative to HABITs, participants in HABITs + Texts will exhibit lower health risk. We hypothesize that this effect will be observed from pre-treatment to post-treatment, pre-treatment to 6-month follow-up, and pre-treatment to 12-month follow-up.

As an Exploratory Aim 1, comparing HABITs and HABITs + Texts, we will examine (a) if the strength of sleep health behavior habit formation mediates the effects of the intervention (specifically by adding the text intervention to HABITs) on improvement in sleep and circadian outcomes, and health-relevant domain outcomes, and (b) if intervention effects are moderated by selected variables (i.e., age, sex, and socioeconomic status).

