### Participants

The inclusion criteria will be as follows: (1) age between 18 and 30, (2) risk for eveningness chronotype: scoring less than or equal to 26 on the Composite Scale of Morningness or a mid-point of sleep later than 4:30 a.m. for 18–24 years of age and 3:50 a.m. for 25–30 years of age on work-free/weekend days over the past month or night-to-night variation in sleep and wake times across one month of 2 h or more, (3) at risk in one of the five health domains: the emotional, cognitive, behavioral, social, or physical domain (at risk is defined as scoring 4 or higher on one item from the Adapted Version of the Work and Social Adjustment Scale), (4) English language fluency, (5) able and willing to give informed consent, and (6) if taking medication for sleep, the dose and frequency of use must have been stable for at least 4 weeks.

Participants will be excluded if they meet any of the following criteria: (1) presence of substance abuse/dependence, mental illness, physical illness, suicidality, or developmental disorder only if it makes participation in the study unfeasible or if there is a significant risk of harm and/or decompensation if treatment of that comorbid condition is delayed due to participating in this study, (2) evidence of sleep apnea, restless legs, or periodic limb movements during sleep (participants presenting with provisional diagnoses of any of these disorders will be referred for a non-study polysomnography evaluation and will be enrolled only if the diagnosis is disconfirmed or if the disorder is treated), (3) night shift worker where the shift is scheduled between the hours of midnight to 6:00 a.m. more than two nights per week, and (4) pregnancy or breast-feeding.

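### The only solicited adverse-event instrument is given once, at post-treatment, and covers only the intervention period, although benefit is tested at 6 and 12 months

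*Protocol article*

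**What the plan says.** Under *Adverse events checklist* (Other measures), the protocol article states: "The Adverse Events Checklist will assess adverse events experienced during the intervention at the post-treatment assessment". The instrument has 16 yes/no items. In Table 4 (*Measures*) the row "Adverse Events Checklist" carries a single mark, which agrees with that text. *Sensitivity analyses* uses the same window: the models are to account for adverse events that occurred during the intervention.

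On timing, *Procedure* says: "At the conclusion of treatment, typically within 8–11 weeks, the post-treatment assessment will take place within 2 weeks of the final session". It then says: "The follow-ups will take place 6 months and 12 months after the pre-treatment assessment".

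On benefit, the hypotheses for all three aims cover change from "pre-treatment to post-treatment, pre-treatment to 6-month follow-up, and pre-treatment to 12-month follow-up". *Background* gives the purpose as to "help participants turn new behaviors into habits and thereby increase the benefits of an intervention in both the short and longer term".

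There is a second route for adverse events, in *Data management and dissemination*: "All adverse events or serious events will be reported to CPHS (i.e., Institutional Review Board), the DSMB, and NICHD". Each DSMB report is also to give the number of adverse or serious events. That section sets no end date for this duty and does not say how events are to be elicited.

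**The concern.** The window for solicited harm does not match the window for claimed benefit. If the intervention works as designed, participants go on performing the behaviours after the coaching ends. Table 2 lists sleep restriction or compression and stimulus control among the helpful habits that may be built. Exposure would then run through follow-up, and benefit is measured there, but the structured question about adverse events is asked only about the weeks in which a coach meets the participant.

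Two things are at stake. First, the main report could make a statement about benefit at 12 months without a harm count obtained by the same method over the same period. A lower count after treatment than during it could simply mean that nobody asked. Second, as more participants move into follow-up, the DSMB's counts for them rest increasingly on what is volunteered or noticed. Volunteered counts cannot be set beside counts from a checklist.

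**Working it through.** The plan gives no figure for the share of the year covered by adverse-event assessment, so there is no stated number to reproduce. The check is a ratio.

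**Inputs**
- Length of treatment: 8–11 weeks (*Procedure*). Nine weekly sessions are planned (*Intervention*), so 9 weeks is used as a middle value.
- Post-treatment assessment: up to 2 weeks after the last session (*Procedure*), so at the latest 11 + 2 = 13 weeks.
- End of observation: 12 months after the pre-treatment assessment (*Procedure*), taken as 52 weeks.
- Assumption: treatment starts at about the pre-treatment assessment. The article does not give the gap.

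**Formula:** share of the year outside the checklist window = (52 − w) / 52, where w is the number of weeks that the checklist covers.

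| Window w | Weeks outside | Share outside |
|---|---|---|
| 8 weeks | 44 | 44/52 = 84.6% |
| 9 weeks | 43 | 43/52 = 82.7% |
| 11 weeks | 41 | 41/52 = 78.8% |
| 13 weeks (stretched to the latest post-treatment visit) | 39 | 39/52 = 75.0% |

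Read literally, the checklist asks about the intervention only, which gives 79–85%. The most generous reading, in which participants also report what happened up to the post-treatment visit, gives 75%.

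**Recall periods if the checklist is repeated.** Take the 6-month assessment as week 26. The interval from a post-treatment visit at week 8–13 is then 26 − 13 = 13 to 26 − 8 = 18 weeks. The interval from the 6-month to the 12-month assessment is 52 − 26 = 26 weeks. The present checklist already asks for recall over about 8–13 weeks.

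**What else is recorded after post-treatment.** Table 4 schedules the DASS, the PHQ, the two PROMIS sleep scales and the Adapted WSAS at 6 and 12 months. These can show worsening in mood, somatic symptoms, sleep and function, and *Aims 1–3* plans to model them by arm. They yield scores on chosen symptoms over their own recall periods (the past 7 days or 4 weeks, where the article states one). They do not record whether a discrete adverse event occurred in the months between assessments.

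**The case against.** The strongest reply is that the gap is narrower than it looks, and much of that reply stands.

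- **A reader might infer that there are no harm data after treatment.** The documents do not support that. The duty to report all adverse and serious events has no stated end, assessors speak with participants by phone or Zoom at 6 and 12 months, and the symptom scales continue to 12 months.
- **A reader might infer that the DSMB's counts leave out everyone in follow-up.** That is not supported either. Events that are volunteered or noticed still count. What the article lacks is a scheduled question that would bring them out.
- **A reader might take exclusion criterion 1 as an admission of late hazard.** It speaks of "significant risk of harm and/or decompensation if treatment of that comorbid condition is delayed due to participating in this study". The delay of other treatment is what is tied to taking part, so the criterion says nothing about harm from the intervention or its habits.
- **The randomised contrast cannot answer the attribution question.** Both arms receive HABITs and differ only in six weeks of texts. Without an untreated control, late events cannot be ascribed to the continued behaviours. Bundles are also individual, typically one or two per participant, so not everyone uses any given technique. This limits what the added data can show. It does not remove the value of describing events and comparing the arms.
- **There is no contradiction, and the article is condensed.** It is true that the checklist section, Table 4 and *Sensitivity analyses* agree with one another. But the checklist's schedule and window are stated outright, so this is a stated choice and not a detail left to a fuller document. How volunteered events are logged may well be set out elsewhere, and no fault is found on that.
- **The percentage is elapsed time, not missed harm.** This is correct, and the figure should be read only in that way.

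**Conclusion.** The point holds as a limit on harm ascertainment. One solicited adverse-event assessment is planned, restricted to the intervention period, while benefit is tested to 12 months. Between 75% and 85% of each participant's 52 weeks has no scheduled adverse-event question. The range depends on treatment length (8–11 weeks) and on whether the window is allowed to run to the post-treatment visit; it assumes that treatment starts near the pre-treatment assessment and that the participant stays to 12 months.

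The primary comparisons of effectiveness are not affected. The consequence is that any longer-term statement weighing benefit against harm would set scheduled benefit measures beside adverse events that were only volunteered. The change is worth making, but the trial's main inference does not depend on it.

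**What to change.** Give the same 16-item checklist at the existing 6-month and 12-month assessments, with the recall period running from the participant's last assessment. Amend the *Adverse events checklist* text and Table 4 to show post-treatment, 6 months and 12 months. Report solicited events by arm in two separate windows, treatment and follow-up, and keep volunteered events distinct from solicited ones. Describe the result as a comparison of HABITs + Texts with HABITs and a description of events, not as harm attributable to HABITs.

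The cost is an amendment and 16 yes/no items at two contacts that blinded assessors already hold by phone or Zoom; no new visit is needed. The downsides are a few minutes' burden, recall of up to about six months at the last assessment, and no follow-up checklist data for participants who have already finished (data collection began in May 2022). The report should therefore state how many participants in each arm were asked at each follow-up.
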